**Fig. 3 Fig3:**
[figure not shown]
The different characteristics of group 1, 2, and 3

Group 1 will start with COPD disease management simultaneous to implementation of the web portal. The web portal is integrated in the disease management program (integrated use).Group 2 is used to working with a COPD disease management program. They will start with the web portal, which is integrated in their own disease management program (integrated use).Group 3 is used to working with a COPD disease management program. They will start with the web portal, but the web portal is not integrated in their own disease management program (free use).

As was described above, the implementation of the portal will be studied using a prospective parallel cohort design. The clinical effects of the web portal will be investigated using an interrupted times series (ITS) study design (Fig. 4) and measured according to changes in health status with the Clinical COPD Questionnaire (CCQ, see Appendix 1). ITS design includes multiple observations over time that are ‘interrupted’ by interventions. The time intervals between the observations T1, T2, T3, and T4 are 6 months, to detect the change in CCQ in a trend and slope over the total period of time. The time intervals between the 3 measurements of each observation T1, T2, T3, and T4 is two weeks, based on the high responsiveness of CCQ [29]. The ITS will be performed according to guidelines of the EPOC Cochrane group [30]. The aim of an ITS design is to detect confounding trends by performing several measurements at specified time intervals, before and after the intervention. An advantage of an ITS design is that it allows for the statistical investigation of potential biases in the estimate of the effect of the intervention.

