### Data collection

Data collection consists of self reporting questionnaires that are integrated in the portal. Therefore all data collection is provided digitally. In Fig. 6 the measurement schedule is visualized. There are four measurements in this study during a period of 16 months. Due to the ITS design, CCQs will be offered three times at each measurement.

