### Power calculation

Health status of patients with COPD generally decreases over time. Recent research on disease management programs in COPD in primary care shows that a general increase of 1.5 to 2.0 points (SD 0.75) in CCQ can be expected during a one year period [37]. In our study we offer patients a web portal in addition to their regular disease management program. We therefore expect that the regular deterioration in CCQ (from 1.5 to 2.0 points) will change to stabilisation of health status at 1.5 CCQ points. Hence, we expect a significant difference in health status of 0.5 points in patients using the portal (2.0-1.5 = 0.5 points). To measure significant differences in health status (>0.5 CCQ points) at 80 % power, SD 0.75 and *α* = 0.05, 37 patients must be included. Based on an estimated 20 % drop-out during the study, 45 (37/0.80) patients are needed. As we use two different organisational implementation methods within two of the care groups 2*45 = 90 patients must be included in those settings. In the third care group only one organisational implementation method (free use) is used. Hence, a total of 225 (90 + 90 + 45) patients are necessary to achieve sufficient statistical power.

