### Data analysis

Along with our research design, analyses will be multilevel:To investigate the effect of the use of the web portal on the primary clinical outcomes, the ITS data will be analysed. The preferred method to analyse ITS studies is a statistical comparison of time trends before and after the intervention. Time series analysis using ARIMA models is one way of analysing the data, but there are a number of statistical techniques that can be used depending on the characteristics of the data, the number of data points available and whether autocorrelation is present. The final choice for the method to analyse the data will be made when the total set of data is available after consultation of a statistician.To investigate the effects of organisational aspects uptake of the portal will be analysed for care group 1, 2 and 3 using Chi Square tests (Fishers’ Exact Test for categorical variables and *F*-tests for continuous variables) and (repeated measures) ANOVA analyses. To analyse the effects of organizational aspects as described in the paper, the groups will be compared.To investigate the effect of integration of the web portal in daily practice, outcomes within integrated (group 1 and 2) and the free use groups (group 3) will be analysed using Chi Square tests (Fishers’ Exact Test for categorical variables and *F*-tests for continuous variables) and (repeated measures) ANOVA analyses.To investigate the effect of different organisational implementation methods, outcomes within groups with high level support (1a and 2a) and low level support (1b, 2b and 3) will be analysed using Chi Square tests (Fishers’ Exact Test for categorical variables and *F*-tests for continuous variables) and (repeated measures) ANOVA analyses.To explore correlation between self efficacy, sociodemographic characteristics on the one hand and adoption of the portal and clinical outcomes on the other hand, Pearson product-moment coefficients will be calculated across all research groups.To make a cost-effectiveness analysis, the direct costs of the different organisational implementation methods will be defined and analysed parallel to the effects of the portal in terms of Quality of Life (EQ-5D).

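### The high versus low support comparison is assigned F-tests and (repeated measures) ANOVA without a baseline covariate; if CCQ is analysed this way, only complete patients count, and completeness may depend on the support level being compared

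*Protocol article*

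**What the plan says.** The Data analysis section treats two kinds of question differently. For the primary interrupted time series it fixes no method: "The final choice for the method to analyse the data will be made when the total set of data is available". For the implementation questions it does name methods. On support level, "outcomes within groups with high level support (1a and 2a) and low level support (1b, 2b and 3) will be analysed" with chi-square or Fisher tests, F-tests "for continuous variables) and (repeated measures) ANOVA analyses". The integrated versus free use comparison gets the same list. No baseline covariate is named for either.

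Three other places bear on how well that method fits:

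- Power calculation: "Based on an estimated 20 % drop-out during the study", 37 patients per cell become 45.
- Methods/Design, text after Fig. 3: observations T1 to T4 lie 6 months apart, and "The time intervals between the 3 measurements of each observation T1, T2, T3, and T4 is two weeks".
- Data collection: "CCQs will be offered three times at each measurement", so each patient is asked for 4 × 3 = 12 CCQs. All questionnaires are built into the portal.

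The Abstract, Methods/Design and Discussion state the hypothesis that more personal support leads to more use of the portal. Support level is randomised within groups 1 and 2; group 3 is not randomised.

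**The concern.** Support level is the only randomised factor in the study, so this comparison deserves the best analysis the data allow. If CCQ is among the outcomes compared, the named method fits the design poorly in three ways.

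- **Incomplete patients.** Classical repeated-measures ANOVA needs a full row per patient. The outcome is recorded through the same portal whose use the support level is meant to change. On the study's own hypothesis, the factor under comparison may therefore influence who supplies complete data. Enlarging the sample replaces lost numbers but does not remove that selection.
- **Baseline.** T1 CCQ is measured three times. In a repeated-measures ANOVA it serves only as one level (or three levels) of time, and in an F-test at follow-up it does not serve at all. Using it as a covariate is the more efficient choice in a randomised comparison.
- **Timing.** The uncorrected group-by-time test assumes sphericity, which equal correlation between all pairs of measurements would satisfy. That is unlikely to hold if scores two weeks apart and scores 6 months or more apart all enter as separate levels.

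**Working it through.** **The plan's own figure.** Inputs from the Power calculation: difference 0.5, SD 0.75, power 80%, α = 0.05 (taken as two-sided). The normal approximation, 2 × [0.75 × (1.96 + 0.84) / 0.5]², gives 35.3, so 36 per group. The exact t calculation gives 79.7% power at 36 and 80.8% at 37, so 37 reproduces. This is a two-group comparison at a single time point, with no baseline or repeated-measures term. With 45 per cell and 20% lost, 45 × 0.80 = 36 remain, with 79.7% power.

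**Completeness.** Assumptions: 20% drop-out from the plan; the first block (or first CCQ) present; and independent extra missingness of 5-10% at each later one (my range, not in the document).

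- All four blocks: 0.80 × 0.95³ = 0.69; 0.80 × 0.90³ = 0.58.
- All twelve CCQs: 0.80 × 0.95¹¹ = 0.46; 0.80 × 0.90¹¹ = 0.25.

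Per cell of 45, that is about 26 to 31 patients (four blocks) or 11 to 20 (twelve CCQs), against the 37 planned. At 31 patients per group the power is 73%, at 27 it is 67%. Pooled over groups 1 and 2 there are 90 per arm, of whom about 52 to 62 have four blocks and 23 to 41 have twelve CCQs. For the pooled contrast with four blocks, selection is therefore a greater worry than numbers.

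**Baseline.** Let ρ be the correlation of T1 with follow-up CCQ, assumed to be 0.5-0.7. Relative to an unadjusted follow-up comparison (variance 1), a change score has 2(1 − ρ) and covariate adjustment has 1 − ρ².

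| ρ | Change score | Covariate | Covariate ÷ change score = (1 + ρ)/2 |
|---|---|---|---|
| 0.5 | 1.00 | 0.75 | 0.75 |
| 0.7 | 0.60 | 0.51 | 0.85 |

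Multiplying 35.3 by these factors and rounding up gives, at ρ = 0.5 and 0.7, 27 and 19 per arm with the covariate, 36 and 22 with change scores, and 36 without adjustment.

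**Sphericity.** Take twelve levels in four blocks, with correlation w within a block and b between any two blocks. Two variances then govern the within-patient contrasts: 1 − w (8 degrees of freedom) and 1 + 2w − 3b (3 degrees of freedom). Epsilon is the squared sum of the 11 values divided by 11 times their sum of squares.

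- w = 0.8, b = 0.7: values 0.2 and 0.5; (1.6 + 1.5)² / [11 × (0.32 + 0.75)] = 0.82. Simulated type I error with 36 per arm is about 6.5%.
- w = 0.9, b = 0.8: values 0.1 and 0.4; (0.8 + 1.2)² / [11 × (0.08 + 0.48)] = 0.65. Simulated type I error is about 8%.
- w = 0.8, with b falling from 0.7 for adjacent blocks to 0.5 for the most distant: epsilon 0.56, type I error about 9%.
- w = 0.8-0.9, with adjacent-block correlation of 0.7-0.8 decaying as a power of the lag: epsilon about 0.3-0.4, type I error about 11-13%.

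The range is thus roughly 6-13% for twelve levels. With four block means it is about 5-8%. In the structures where it was checked, a Greenhouse-Geisser correction brought the twelve-level test back to about 4-5%, and the between-arm main effect stayed at about 5%.

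**The case against.** The case against is substantial, and much of it limits the point.

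- **Scope.** The hypotheses for the implementation comparison concern use and satisfaction. CCQ effects are assigned to the time-series analysis within each care group. The support comparison refers only to outcomes, and repeated measures stands in brackets. This stands: the point is conditional on CCQ being analysed there, which the wording allows but does not state. A reader might infer that the primary analysis is at fault. It is not, because its method is open.
- **Dropped patients.** A reader might infer that the plan says incomplete patients are excluded. It does not; exclusion follows from the classical method. Missing-data detail may properly sit in an analysis plan that is not shown. But the article names the method itself, so the method can be judged. The allowance for 20% drop-out covers numbers, not selection related to the arm.
- **Baseline unused.** This would be too strong. T1 enters a repeated-measures ANOVA as a level of time, and the group-by-time test uses it. Only a plain follow-up F-test ignores it.
- **Sphericity violated.** This too would be too strong. Nothing says that all twelve CCQs are separate levels, and four block values are an equally natural reading. The effect touches only the time and group-by-time terms, and a routine correction, which a condensed article need not mention, repairs it. Figures of 11-13% hold only with strong within-block or decaying between-block correlation.
- **Group 3.** Groups 1 and 2 differ from group 3 in portal, training and organisation. Baseline adjustment there is not a free gain in precision, so the remedy must be confined to the randomised groups.

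**Conclusion.** The point holds in a limited form: for the support comparison, the article names a method that is weaker than one available at no cost in data. The strongest ground is the complete-patient requirement in a setting where outcome collection runs through the portal and support is expected to change its use. Under the assumed 5-10% extra missingness, 31-42% of patients would be lost with four blocks and 54-75% with twelve CCQs. Whether this biases the comparison depends on whether the losses differ by arm and relate to CCQ, which the document cannot show. The second ground is efficiency: not using T1 as a covariate gives up 25-49% of the variance against a follow-up comparison, or 15-25% against change scores, for ρ of 0.5-0.7. Sphericity is a minor third ground that depends on the analysis unit and on the absence of a correction. The correlations and extra missingness are assumptions; only the 20% drop-out and the timing come from the protocol. This should be changed, but it does not undermine the primary analysis.

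**What to change.** In the support comparison of CCQ, and of EQ-5D where a baseline exists, replace (repeated measures) ANOVA by a likelihood-based linear mixed model:

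- all available T2-T4 values, so that partly complete patients contribute (valid if data are missing at random given what is observed);
- the baseline value as covariate, for CCQ the mean of the three T1 scores, assuming T1 precedes portal start;
- fixed effects for care group, support, time and support-by-time;
- a covariance that allows for the block timing (two weeks within a block, 6 months between blocks).

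Estimate the support effect within randomised groups 1 and 2, and report it with a 95% CI at one block named in advance. Report the comparison with group 3 separately and label it observational. Analyse MRC grade with an ordinal method.

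The cost is a change of wording and a slightly more complex model. No new data are needed.

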### Recruitment of patients and non-participation analysis

We started by recruiting primary care groups; group 1, group 2, and group 3 decided to participate in this study because they wanted to contribute to a project with a possible healthcare improvement. The general practitioners that are part of the care groups could volunteer to participate in the study; a selection of them did.

Because general practices as well as patients are free to volunteer, bias might occur in our research group. We will determine the differences in clinical status between study participants (included patients) and non-participants (eligible patients) by CCQ questionnaire, as well as gender and age differences.

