**Fig. 5 Fig5:**
[figure not shown]
Interventions per group

In group 1 all caregivers (GPs as well as practice nurses) will be trained to provide COPD care according to an evidence based disease management program; subsequently they implement the COPD care program in their practices under supervision of a specialized nurse. Practice nurses will receive support by a research nurse to make sure their records of COPD patients are up-to-date and to prepare consultation with their patients according to the disease management program. In addition, all practice nurses will be trained to use the web portal and to communicate with patients according to the principles of self-management.In group 2 all caregivers (GPs as well as practice nurses) will be trained shortly to ameliorate their skills in COPD care according to an evidence based disease management program that they already use. All practice nurses will be trained to use the web portal and to communicate with patients according to the principles of self-management. The training is developed and provided for by the e-Vita study group and is based on national and international guidelines.In group 3 caregivers will not receive any training. Patients will receive a brochure how to use the web portal.

The type of intervention is adopted by the care groups after thorough consideration and discussion. The e-Vita study group determined the type of platform and the level of support.

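### The care-group and integrated-versus-free-use comparisons lie wholly between general practices but are tested as if patients were independent, so their standard errors are too small

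*Protocol article*

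**What the plan says.** All places are in the protocol article.

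- **Data analysis.** Uptake of the portal is compared across care groups 1, 2 and 3 with chi-square or Fisher's exact tests, F-tests and (repeated measures) ANOVA. The same tests serve the integration question: "outcomes within integrated (group 1 and 2) and the free use groups (group 3) will be analysed using Chi Square tests". No practice term or clustered error is named. Only the method for the interrupted time series is left open, pending advice from a statistician.
- **Recruitment of patients and non-participation analysis.** Practices select themselves: "The general practitioners that are part of the care groups could volunteer to participate in the study".
- **Intervention.** "In group 1 all caregivers (GPs as well as practice nurses) will be trained" in the disease management programme; group 2 caregivers get a shorter training and group 3 caregivers none. In groups 1 and 2 the patient's own practice nurse holds the intake, agrees a personal health goal and explains the portal.
- **Methods/Design.** Only level of support is randomised, by patient, within groups 1 and 2. Care group and integration are not randomised.
- **Power calculation.** The sample size is built per implementation arm for a portal effect: "we expect a significant difference in health status of 0.5 points in patients using the portal".

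**The concern.** Patients of one practice share a nurse, a training history and local routines, so their portal use and outcomes are likely to resemble each other. The article's own Discussion expects this: it hypothesises that skilled and motivated nurses and doctors lead to more portal use and so to better health status.

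A comparison of care groups, or of groups 1 and 2 with group 3, sets one collection of practices against another. Practice-to-practice variation therefore enters the difference in full. Chi-square tests, F-tests and ordinary ANOVA leave it out of the error term. Repeated-measures ANOVA handles correlation within a patient, not within a practice.

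The heading statement that analyses will be *multilevel* does not settle this. No hierarchical model follows it, and Methods/Design uses the word for having several purposes.

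At stake are the conclusions about organisation and integration, which are a declared aim of the study. Differences between care groups would be called significant more often than the nominal level allows.

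**Working it through.** **1. The plan's own figure.** The inputs from the Power calculation section are a difference of 0.5 points, "at 80 % power, SD 0.75" and alpha 0.05. For two independent groups, two-sided:

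n per arm = 2 × (0.75/0.5)² × (1.96 + 0.84)² = 2 × 2.25 × 7.84 = 35.3, so 36 by the normal formula.

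With the t distribution, power is 79.7% at 36 and 80.8% at 37. The stated 37 is thus the formula for independent patients, with no clustering allowance. (The drop-out step, 37/0.80 = 46.25 but stated as 45, is a separate matter and does not enter here.)

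**2. Which comparisons lie between practices.**

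| Comparison | How formed | Position relative to practices |
|---|---|---|
| Care groups 1, 2, 3 | not randomised | wholly between |
| Integrated (1, 2) vs free use (3) | not randomised | wholly between |
| High (1a, 2a) vs low support (1b, 2b, 3) | randomised by patient in groups 1 and 2, group 3 added | mostly within |

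**3. Inflation for the first two rows.** With m patients per practice:

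- design effect DE = 1 + (m − 1) × ICC
- the naive standard error is too small by the factor √DE
- true two-sided level of a nominal 5% two-group test = 2 × [1 − Φ(1.96/√DE)]

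Neither m nor the ICC is in the article, so the values below are assumptions.

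| m | ICC | DE | √DE | 1.96/√DE | True level |
|---|---|---|---|---|---|
| 5 | 0.02 | 1.08 | 1.04 | 1.89 | 5.9% |
| 10 | 0.02 | 1.18 | 1.09 | 1.80 | 7.1% |
| 5 | 0.05 | 1.20 | 1.10 | 1.79 | 7.4% |
| 5 | 0.10 | 1.40 | 1.18 | 1.66 | 9.8% |
| 10 | 0.05 | 1.45 | 1.20 | 1.63 | 10.4% |
| 10 | 0.10 | 1.90 | 1.38 | 1.42 | 15.5% |

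**4. The support comparison.** Take 37 completers per cell: 74 high support against 111 low support (74 from groups 1 and 2, 37 from group 3). Assume both levels are split evenly within each practice.

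- Each of the 148/m practices in groups 1 and 2 enters with net weight (m/2) × (1/74 − 1/111) = m/444. Together they contribute (148/m) × (m/444)² = 0.00075m.
- Each of the 37/m practices in group 3 has weight m/111. Together they contribute (37/m) × (m/111)² = 0.00300m.
- The sum is 0.00375m, against 1/74 + 1/111 = 0.02252 under independence. The ratio is m/6.

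So DE = (1 − ICC) + ICC × m/6 = 1 + ICC × (m/6 − 1). For m of 5 to 10 and ICC of 0.05 to 0.10 this runs from 0.98 to 1.07, with a true level of 4.8% to 5.8%.

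**5. Power of the between-practice comparisons.** For a 0.5-point difference, SD 0.75, a two-sample t test and sample sizes divided by DE:

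| Comparison (completers) | DE 1 | 1.2 | 1.45 | 1.9 |
|---|---|---|---|---|
| Integrated vs free (148 vs 37) | 95% | 91% | 85% | 74% |
| Group 1 vs 2 (74 vs 74) | 98% | 96% | 92% | 83% |
| Group 1 vs 3 (74 vs 37) | 91% | 85% | 78% | 66% |

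**The case against.** **Power.** A reader might infer that the stated 80% power fails for these comparisons. The article does not support that. It claims 80% for a 0.5-point portal effect per implementation arm, not for a contrast between care groups. Nor does any between-care-group contrast have 37 against 37 patients; most combinations in step 5 stay above 80%. The Power calculation section needs no rewriting on this account.

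**Support.** A reader might extend the inflation to high versus low support, because group 3 is added to the low side. Step 4 shows that the test stays close to 5% if both levels occur in each practice. Adding group 3 raises a question of confounding, not of this variance.

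**Size is assumed.** This stands. The 16% end needs both upper assumptions; at an ICC of 0.02 the true level is 6% to 7%. Nurse delivery is also absent in group 3, so a single design effect for all groups is a simplification. Group 3 patients nevertheless belong to practices as well.

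**Change measures.** In a repeated-measures analysis of health status, stable practice differences largely cancel, so the relevant ICC may be small. That is fair, but practice differences in change remain, and portal uptake has no pre-portal value to cancel against.

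**Limited value.** There is one care group per condition, and Methods/Design itself says the cohorts cannot be compared by combining data across groups. So correcting precision does not make the contrasts causal. That limits how much the point matters, but does not justify error bars that are too narrow.

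**Left to the analysis plan.** A condensed article may leave error structure to a fuller document. Here, however, the tests are named, and they are single-level.

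**Conclusion.** The point holds for two comparisons: care groups 1, 2 and 3, and integrated versus free use. The named tests ignore practice, and both contrasts lie entirely between practices, so any positive practice ICC makes the standard errors too small. The direction is certain given a positive ICC; the size is not. With 5 to 10 patients per practice and an ICC of 0.02 to 0.10, both assumed, standard errors are too small by a factor of about 1.04 to 1.38, and a nominal 5% two-group test runs at about 6% to 16%.

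The finding does not reach the stated 80% power, the randomised support comparison, or the interrupted time series analysis of the primary outcome, whose method is left open.

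**What to change.** In the Data analysis section, for the two comparisons named:

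- Replace the single-level tests with a mixed model (a generalised mixed model for uptake and other categorical outcomes) with a random intercept for practice. Where measurements repeat, keep a patient-level term as well. Practice-clustered standard errors with a small-sample correction are an acceptable alternative.
- Report the results as descriptive estimates with intervals, and say that a practice term corrects precision only. It cannot separate integration from the differences in portal, training and programme between care groups.

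The cost is a practice identifier in the data set and somewhat wider intervals. No extra patients and no change in study conduct are needed.

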## Methods/Design

Our primary aim is to investigate the effect of use of patient portals on clinical outcomes in primary care COPD patients (net benefits, Fig. 1). In addition, we aim to investigate the optimal organisational implementation method of the platform. Therefore we will compare different organisational implementation methods in different care settings, and evaluate their use and user satisfaction. We hypothesize that an implementation setup with greater personal support, integrated into an existing care programme will be preferred by patients and therefore be more likely to be used.

As discussed in the introduction, the evaluation of eHealth is a challenge because of the different views to evaluate from (clinical, technical, and organisational). Moreover, eHealth is not a classical clinical isolated intervention (in this case a platform) with one output (here CCQ). Instead it affects care processes, communication and patients behaviour, Finally we have a multilevel purpose to not only investigate effects but also organisational implementation methods. Therefore we made a design for a quality improvement intervention. In this study we aimed to include the importance of integration in the daily practice of primary care. Therefore we chose an implementation study [25]. We designed a method to promote the uptake of our research findings into routine primary healthcare; with this design we aim at studying the influences on healthcare professionals and patient behaviour and at evaluating the process by which effects are achieved.

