**Fig. 2 Fig2:**
[figure not shown]
Research design for the different groups and interventions of e-Vita COPD

Organisational and technical differences are depicted in Fig. 2: three different care groups and two different web portals are included. Two different methods of implementation are distinguished within group 1 and 2: one with high level of personal assistance and one with low level of personal assistance. All patients in group 1 and 2 start with a personal instruction by the primary care nurse during a regular control visit. Patients will be randomly subdivided in two groups by computer by research assistants (randomisation is computerised to prevent human influence) with high (a) and low (b) level of support. In group 1a, high level support implies home visits for patients by a research nurse who accompanies the use of the web portal. In group 2a, high level support implies telephone consultation for patients by a research nurse who accompanies use of the web portal. In group 1b and 2b low level support implies that the primary care nurse shows the patient only once how to use the web portal (the usual organisational implementation method in daily practice) without any follow-up instruction. In group 3 the web portal is offered as free use: patients will receive instructions from the web portal itself. There will be no active support from caregivers or research nurses.

The groups differ in organisation, area, use of the web portal, and integration of the portal in a COPD disease management program (Fig. 3); these characteristics are based on Dutch reports of care groups [28]:

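### The integration comparison (groups 1 and 2 against group 3) counts half of any effect of the randomised extra support as an effect of integration

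*Protocol article*

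**What the plan says.** The Data analysis section of the protocol article defines the integration analysis by its cells: "outcomes within integrated (group 1 and 2) and the free use groups (group 3) will be analysed", using chi-square or F tests and repeated-measures ANOVA. It names no support term and no restriction to low-support patients.

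The text around Fig. 2 (Methods/Design) describes the randomised support inside the integrated pool:
- Arm 1a: "In group 1a, high level support implies home visits for patients by a research nurse who accompanies the use of the web portal".
- Arm 2a: "In group 2a, high level support implies telephone consultation for patients by a research nurse".
- Arms 1b and 2b: one demonstration by the primary care nurse and no follow-up.
- Group 3: no active support from caregivers or research nurses.

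Support has its own comparison in Data analysis: "outcomes within groups with high level support (1a and 2a) and low level support (1b, 2b and 3) will be analysed".

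The hypothesis in Methods/Design reads: "We hypothesize that an implementation setup with greater personal support, integrated into an existing care programme will be preferred by patients". The text around Fig. 3 says "Group 1 will start with COPD disease management simultaneous to implementation of the web portal". Group 2 already worked with such a programme, and of the comparator it says "Group 3 is used to working with a COPD disease management program".

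**The concern.** The pool called integrated differs from group 3 in a second factor that the trial itself assigns: follow-up support. The Discussion expects greater personal support to increase use of the portal. If that is right, the integration contrast shifts in favour of integration even when integration does nothing. Finding the best way to implement the portal is a stated aim, so a care group could be advised to integrate the portal when the gain came from home visits or telephone calls.

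A second and distinct confounder sits in the same contrast. The hypothesis concerns integration into an existing programme, but group 1 has none at the start. Whatever the launch of the programme does in group 1 is also counted as integration. This is not part of the support effect and needs its own remedy.

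**Working it through.** **Planned sizes (Power calculation section).** The inputs are a difference of 0.5 CCQ points, SD 0.75, power 80% and alpha 0.05, giving 37 patients.
- Normal approximation, two-sided, two samples: 2 × (1.960 + 0.842)² × 0.75² / 0.5² = 35.3, so 36 per arm.
- The two-sample t-test gives 36.3, so 37. The stated figure reproduces as a per-arm size.
- After dropout the plan uses 45 per arm: 90 in group 1, 90 in group 2 and 45 in group 3, total 225.
- The document gives no figure for the integration comparison itself.

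**What the pooled contrast estimates.** Let L1, L2 and L3 be the means at low support in groups 1 and 2 and in group 3, and let s1 and s2 be the support effects in groups 1 and 2. With 45 patients per arm:

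- Pooled mean = [45(L1 + s1) + 45·L1 + 45(L2 + s2) + 45·L2] / 180 = (L1 + L2)/2 + (s1 + s2)/4
- Contrast = (L1 + L2)/2 − L3 + (s1 + s2)/4

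With s1 = s2 = s, the support term is s/2, which is the share 90/180 times s. If launching the programme shifts group 1 by g (L1 = L2 + g), a further g/2 enters.

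**Size on portal use.** The document gives no usage rates. Assume 40% use at low support and in group 3, no integration effect and no other difference between groups. The test is the two-sided 5% chi-square test at 180 v 45, by simulation.

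| Assumed support effect | Spurious difference | Significant |
|---|---|---|
| +10 points | 5 points | about 9% |
| +20 points | 10 points | about 22% |
| +30 points | 15 points | about 44% |

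**Size on CCQ.** SD 0.75 is from the Power calculation section. The support effects, as points of improvement, are assumed. SE = 0.75 × √(1/180 + 1/45) = 0.125. After 20% dropout (144 v 36), SE = 0.75 × √(1/144 + 1/36) = 0.140.

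| Assumed support effect | Bias | Significant, 180 v 45 | Significant, 144 v 36 |
|---|---|---|---|
| 0.10 | 0.05 | 7% | 6% |
| 0.25 | 0.125 | 17% | 15% |
| 0.40 | 0.20 | 36% | 30% |
| 0.50 | 0.25 | 52% | 43% |

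A programme-start effect of an assumed 0.25 points in group 1 would by itself add 0.125.

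**Price of restricting to 2b v 3.** The SE ratio is √(2/45) / √(1/180 + 1/45) = 0.2108/0.1667 = 1.265. Power for 0.5 CCQ points is 89% at 45 v 45 and 81% at 36 v 36, against 98% and 95% for the pooled contrast.

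All of these figures treat patients as independent at one time point; practice clustering and repeated measures are ignored.

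**The case against.** **Integration cannot be isolated in this design anyway.** This stands. Group 3 is a different care group, has a portal of lower quality and has no caregiver training (Intervention section). Arm 2b also receives a personal nurse instruction and a goal-setting intake that group 3 does not. A reader might infer that 2b v 3 is a clean test of integration with a 5% false-positive rate. The rate would be about 5% only if every one of these differences had no effect, and the document gives no ground for that. The restriction removes the follow-up support that the trial assigns, and nothing else. That is still worth doing, because this part can be avoided at almost no cost.

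**Support and integration can be told apart.** This also stands. A reader might infer that the two are inseparable, but support is randomised within groups 1 and 2, so its effect can be estimated from 1a v 1b and 2a v 2b. The planned support comparison does not repair the integration contrast, however. It places group 3 among the low-support patients (45 of 135), so one third of any group 3 difference enters it in turn.

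**The comparison of uptake across care groups 1, 2 and 3 might seem to share the fault.** It does not in the same sense. The plan labels it as organisational aspects, and support level is one of these, so nothing there is mislabelled as integration.

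**A full analysis plan could add a support term.** It could, and a condensed article need not give model details. But the article names the cells to be compared, and a plan that followed it would inherit the pooling.

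**The hypothesis in Methods/Design is a joint one.** It does describe support and integration as one set-up. The expectation that support alone raises use is in the Discussion. Data analysis nevertheless sets up a separate test of integration, and that test is what is at issue.

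**Conclusion.** The point holds. As defined, the integration contrast contains half of the average support effect and, separately, half of any programme-start effect in group 1. Both weights follow from the planned arm sizes. How much this matters depends on effects that the document does not give. Under the assumptions above, the chance of a spurious integration finding on portal use runs from about 9% to 44%; at the low end the inflation is modest.

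The contrast is secondary and non-randomised. A reader might infer that the primary result is compromised, but the clinical effect on CCQ is analysed by interrupted time series within each care group and does not use this comparison. Severity: should-fix.

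**What to change.** Change the Data analysis wording as follows:

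1. Make the integration comparison at low support only. Use 2b v 3 as the main contrast, since both have an existing programme and neither has follow-up support. Show 1b v 3 separately, as integration with a newly started programme.
2. Alternatively, fit all five arms with care-group terms and a support term nested in groups 1 and 2, and read the integration comparison as group 2 at low support against group 3.
3. Estimate the support effect from the randomised contrasts 1a v 1b and 2a v 2b, leaving group 3 out.
4. Label the integration result as descriptive, and list the remaining differences between 2b and 3: care group, portal quality, caregiver training, and nurse instruction and intake.

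The change needs no new data or patients. The price is precision: 45 v 45 instead of 180 v 45, with a standard error about 26% larger.
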